## Protocol

### Study objectives and hypotheses

*Overall hypothesis*

Wasting malnutrition at any age has medium- and long-term detrimental effects on endocrine and exocrine pancreatic function and structure.
1.
**
*Specific objective 1*:** To investigate whether wasting malnutrition at various ages is associated with abnormalities of pancreas structure and function later in life.a.
**
*Hypothesis 1*:** Prior wasting malnutrition is associated with later abnormal pancreatic structure and endocrine and exocrine function.b.
**
*Pancreatic phenotype of interest:*
** Diabetes assessed by oral glucose tolerance test (OGTT) and haemoglobin A1c (HbA1c), exocrine pancreatic function tests (serum lipase, faecal elastase), pancreatic size and architecture measured using ultrasound for all participants and measured using computed tomography (CT) scans for a subset of participants (non-pregnant adult participants).2.
**
*Specific objective 2:*
** To investigate whether pancreatic abnormalities in participants with prior malnutrition and diabetes are analogous to a previously described entity of fibro-calculous diabetes.a.
**
*Hypothesis 2:*
** Prior wasting malnutrition is associated with pancreatic calcification which in turn is associated with diabetes.b.
**
*Pancreatic phenotype of interest:*
** Pancreatic calcifications determined from CT scans among non-pregnant adult study participants.3.
**
*Specific objective 3:*
** To investigate the relative importance of decreased insulin production or increased insulin resistance in malnutrition-associated diabetes.a.
**
*Hypothesis 3:*
** The abnormal glucose regulation seen after wasting malnutrition is associated with relative insulin deficiency with or without insulin resistance.b.
**
*Pancreatic phenotype of interest:*
** Indices of glucose metabolism and insulin kinetics based on mathematical models of glucose and hormone concentrations during OGTT and intravenous glucose tolerance tests (IVGTT). Homeostasis model assessment of insulin resistance (HOMA-IR) and liver fat (insulin resistance) will also be assessed.4.
**
*Specific objective 4:*
** To investigate whether a prior abnormal pro-insulin/insulin ratio is associated with diabetes in adults infected or not with HIV or previously with tuberculosis.a.
**
*Hypothesis 4:*
** An abnormal pro-insulin/insulin ratio is associated with later development of diabetes in adults who had malnutrition earlier in life in association with HIV or tuberculosis infection.b.
**

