**3.**	** *CICADA (Chronic Infections, Co-morbidities and Diabetes in Africa), Mwanza, Tanzania* ** The CICADA cohort, ^ 17 ^ total n=1947, comprises three subgroups: a) Tuberculosis patients and controls from the TB-NUT study whose HIV and nutritional status ~16 years ago at recruitment are known (50% BMI<18.5 kg/m ^2^) as well as more recently recruited HIV-infected and uninfected people (controls) ^ 18 ^ ^,^ ^ 19 ^ b) NUSTART, conducted 2010-2014, was a two-site (Mwanza and Lusaka) trial of food supplements for malnourished (BMI<18.5 kg/m ^2^) HIV-infected adults, recruited when starting antiretroviral therapy. ^ 20 ^ In Mwanza, 704 participants were recruited, 409 were alive and followed at the 12-week NUSTART end-point; 273 were available at a follow-up two-three years after starting ART and 206 were recruited to the CICADA study. c) HIV-infected and uninfected people, both malnourished and well-nourished, recruited 3-four years ago for HIV, nutrition and diabetes assessments *CICADA has the most detailed longitudinal diabetes data of the project cohorts, archived fasting samples, and are the oldest so have had longer to develop diabetes; therefore, this cohort will be used for the in-depth and longitudinal components.*	CICADA (TB-NUT) 16 y prior: 450 total • 73 (16.2%) BMI <17 kg/m ^2^ • 74 (16.4%) BMI 17 to 18.5 kg/m ^2^ • 303 (67.4%) BMI > 18.5 kg/m ^2^ CICADA (NUSTART) 11 y prior: 208 total • 105 (50.5%) BMI <17 kg/m ^2^ • 103 (49.5 %) BMI 17 to 18.5 kg/m ^2^ CICADA (New HIV +/- cohort) 4 y prior: 1293 total • 109 (8.4%) BMI <17 kg/m ^2^ • 171 (13.3 %) BMI 17 to 18.5 kg/m ^2^ • 1009 (78.3%) BMI >18.5 kg/m ^2^ Expected for SAMPA: 1412 total
**4.**	** *NUSTART, Lusaka, Zambia* ** 200 previously malnourished HIV-infected adults will be traced and recruited from the NUSTART Lusaka participants. ^ 20 ^ We will also recruit 50 HIV-infected and 50 non-HIV-infected, not previously malnourished, neighbourhood controls.	• 10 y prior: 1111 total, 437 (39%) BMI 17 to 18.5 kg/m ^2^, 674 (61%) BMI<17 kg/m ^2^ • Expected for SAMPA: 300 total

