### Outcome measures

*Primary outcome measures*
1.Pancreatic endocrine function: diabetes or impaired glucose tolerance (pre-diabetes) by OGTT or HbA1c, defined using World Health Organization (WHO) cut-offs
^
23
^
2.Pancreatic exocrine function: faecal elastase and serum lipase

*Secondary outcome measures*
1.Pancreas size and structure: Pancreas size and architecture using ultrasound and CT (subsets from all adult cohorts)2.Pancreatic calcification: Calcification determined by CT scan (subsets from all adult cohorts)3.Insulin production and insulin resistance:a.Mathematical modelling of blood glucose, insulin and C-peptide at three (for children) or seven (for adults) times during a 120-minute OGTT for estimation of indices of first phase, second phase and total insulin release, insulin kinetics and insulin resistance;b.Mathematical modelling of data from analytes from IVGTT measured in blood samples collected at -10, -1, 2, 4, 6, 8, 10 minutes: glucose, insulin, and C-peptide (subset from CICADA
*).*
4.Other hormonal contribution to glucose metabolism and diabetes: Incretins (gastric inhibitory polypeptide (GIP) and glucagon-like peptide-1 (GLP-1)) and glucagon at 0, 30, 60, 90 and 120 minutes during an OGTT (subsets from CICADA and St-ATT). The goal is to assess whether insulin resistance is associated with changes in endocrine signals from the gut. The area under the curve of glucagon (AUC glucagon) will be used to assess a possible presence of hyperglucagonemia, often seen in T2D subjects.5.Proinsulin: Proinsulin in baseline samples before OGTT. The baseline proinsulin levels will be used as indicator of β-cell stress/exhaustion in the fasting state where higher levels of proinsulin will indicate higher levels of β-cell stress.6.Abnormal prior pro-insulin/insulin ratio and diabetes (subset): From the CICADA cohort, measurement of pro-insulin and insulin in fasting samples collected four years previously and comparison with current diabetes by OGTT. Like the fasting proinsulin, the pro-insulin/insulin ratio in fasting samples will be used as a surrogate measure of β-cell stress.

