^3^)•Abnormalities in duct size•Presence of cysts or calcification.Standardisation of the measurements between sites will be assured by consultation among all site radiologists of 10 scans from each cohort. The studies will be conducted and reviewed for incidental findings at the local site in accordance with the relevant standard operating procedure (SOP).11.
**
*Proinsulin-insulin ratio*
**: This will be done in 120 archived samples from the CICADA cohort which were collected from fasting participants about four years prior to the SAMPA visit.

The DIVIDS child cohort will not have CT scans but 100 children will have MRI scans, funded through a separate project, which will permit examination of pancreas size and structure as well as quantification of visceral fat. Also, in the DIVIDS cohort only, we will measure full blood count, blood lipids and C-reactive protein in baseline samples from the OGTT; this is done for purposes of local ethics and family desire for the information.

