A deeper understanding of associations between prior malnutrition and the underlying glucose metabolic pathways will be explored through modelling biochemical measures over the course of the two-hour OGTT. Glucose, insulin and C-peptide data from OGTT will be used to model pancreatic cell functionality according to published methods in order to determine a set of indices quantifying: first phase, second phase, and total insulin secretion,
^
37
^ whole-body and hepatic insulin clearance,
^
38
^ and insulin sensitivity.
^
25
^
^,^
^
39
^ For the child cohorts for whom only three blood samples are available over the two-hour OGTT, we will use methods designed to determine insulin sensitivity from sparsely sampled OGTTs.
^
26
^ The IVGTT data from the CICADA cohort subset can be similarly modelled to estimate insulin sensitivity and insulin secretion. Comparison of the indices estimated from the two tests will provide information as to whether altered intestinal function,
*e.g.* glucose absorption or incretin secretion, influences insulin secretion or sensitivity in participants previously malnourished or not.

**
*Sample size*
**: We will use individual data from all SAMPA adult participants and, for children who have only three sample points during OGTT, we will combine data from groups of participants.
^
26
^ Most previous studies in this area include 10-100 people per group, whereas we will be able to study all SAMPA participants.

*Hypothesis 4:*
An abnormal fasting pro-insulin/insulin ratio is associated with later development of diabetes in adults who had malnutrition and infection.

**
*Analysis*
**: We will use the detailed data and samples available from CICADA to investigate whether the proinsulin/insulin ratio in CICADA samples collected from fasted participants about four years prior to the SAMPA visit is associated with diabetes or prediabetes at the SAMPA visit. This will be a nested case-control study where cases are 60 CICADA participants with current diabetes by OGTT and controls are 60 CICADA participants with normal OGTT. These participants will be selected by stratified random sampling. Logistic regression will be used, controlling for age and sex, to determine if prior proinsulin/insulin ratio is associated with later diabetes.

**
*Sample size*

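### The Hypothesis 4 model adjusts only for age and sex, although low BMI and HIV status at the time of the archived sample may confound the link between the proinsulin/insulin ratio and later diabetes

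*Protocol article*

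**What the plan says.** Under Statistical analyses and sample size calculations, Hypothesis 4 compares 60 CICADA participants with diabetes and 60 with a normal OGTT, chosen by stratified random sampling with the strata not named. The model is given in one sentence: "Logistic regression will be used, controlling for age and sex, to determine if prior proinsulin/insulin ratio is associated with later diabetes". No further step follows. Under Hypothesis 1, by contrast, age and sex are only the initial adjustment, and HIV status, BMI, fat mass and diet are examined afterwards.

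The timing of the ratio is stated three times: "measurement of pro-insulin and insulin in fasting samples collected four years previously and comparison with current diabetes by OGTT" (Outcome measures), "collected from fasting participants about four years prior to the SAMPA visit" (Assessments, item 11) and "collected from fasted participants about four years prior to the SAMPA visit" (Hypothesis 4, Analysis).

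Table 1 describes the newest CICADA subgroup as "HIV-infected and uninfected people, both malnourished and well-nourished, recruited 3-four years ago for HIV, nutrition and diabetes assessments" and gives its BMI distribution under "CICADA (New HIV +/- cohort) 4 y prior: 1293 total". The TB-NUT and NUSTART members' BMI dates from 16 and 11 years earlier.

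Hypothesis 4 itself concerns diabetes "in adults who had malnutrition earlier in life in association with HIV or tuberculosis infection". The Introduction says that BMI and infections able to affect the pancreas will be taken into account, and the legend of Figure 1 lists BMI and HIV status as possible modifiers.

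**The concern.** For TB-NUT and NUSTART members the recorded malnutrition came about 12 and 7 years before the archived sample (16 − 4 and 11 − 4). For the newest subgroup the two dates coincide. One model therefore pools people whose ratio was measured long after malnutrition with people who apparently had low BMI when the blood was drawn.

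If body mass or HIV infection at that visit alters fasting proinsulin or insulin, and also bears on later diabetes, part of any association between ratio and diabetes reflects those conditions. The protocol reads the ratio as a marker of beta-cell stress that comes before diabetes. A model with only age and sex leaves that reading open to an alternative explanation which data apparently already on file could address.

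**Working it through.** **1. The plan's own power figure.** Inputs from Hypothesis 4, Sample size: 60 per group, difference 0.04, SD 0.07. Two-sided alpha of 0.05 is assumed because none is stated.
- Standard error = 0.07 × √(2/60) = 0.01278.
- 0.04 / 0.01278 = 3.130, and power = Φ(3.130 − 1.960) = 87.9%, against the stated 90%.
- The difference detectable with 90% power is 0.0414, so rounding to 0.04 explains the gap. The point does not depend on it.

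**2. How many had low BMI at about the time of the sample.** Counts from Table 1, BMI up to 18.5 kg/m²:
- TB-NUT: 73 + 74 = 147, recorded 16 years before.
- NUSTART: 105 + 103 = 208, recorded 11 years before.
- Newest subgroup: 109 + 171 = 280, recorded 4 years before.
- Total 635. 280/635 = 44% of recorded malnourished members; 280/1293 = 21.7% of the newest subgroup; 280/1951 = 14.4% of all CICADA (450 + 208 + 1293 = 1951).

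Hypothesis 4 samples by diabetes status from CICADA, so 14% is the more relevant share. BMI at the four-year visit is not given for TB-NUT and NUSTART members, so the true share with low BMI at sampling is unknown.

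**3. Possible size of the bias.** The document gives no effect of BMI or HIV on the ratio, so these are assumptions:
- q, the share with low BMI at sampling: 14.4% or 21.7%.
- Outcome risk 7% without low BMI, and 10%, 14.5% or 16% with it. These borrow the Hypothesis 1 figures: 7% baseline, an absolute difference of 3% to 9% in earlier studies, and 7.5% as the detectable difference. They concern OGTT glucose of 7.8 mmol/L or more, or raised fasting glucose, and only stand in for diabetes risk here.
- Shift in the ratio with low BMI: 0.02, 0.04 or 0.07 (the last is 1 SD).

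With a and b the risks without and with low BMI:
- share among cases = qb / [qb + (1 − q)a]
- share among controls = q(1 − b) / [q(1 − b) + (1 − q)(1 − a)]
- spurious difference = shift × (share in cases − share in controls)

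For 14.5% v 7%, low BMI is present in 26% of cases and 13% of controls (q = 14.4%), or 37% and 20% (q = 21.7%):

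| Shift | Spurious difference | Share of 0.04 | Type I error |
|---|---|---|---|
| 0.02 | 0.0025–0.003 | 6–8% | 5.4–5.7% |
| 0.04 | 0.005–0.0065 | 12–16% | 6.8–8.0% |
| 0.07 | 0.009–0.011 | 22–28% | 10.5–14.3% |

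At 10% v 7% with a shift of 0.02 the bias is 0.001 (3–4% of the target). At 16% v 7% with a shift of 0.07 and q = 21.7% it is 0.013 (33%). It is zero if low BMI does not shift the ratio or is balanced between cases and controls.

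**4. The opposite direction.** Suppose low BMI halves the risk (3.5% v 7%), q = 21.7% and the shift is 0.07. The shares are 12.2% of cases and 22.3% of controls, so the bias is 0.07 × (−0.102) = −0.007. A true difference of 0.04 (0.57 SD) would appear as about 0.033 (0.47 SD).

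**5. Cost of adjustment.** Effective group size = 60 × (1 − R²), where R² is the assumed share of variation in common with the added terms. Power is 86.2% at R² = 0.05, 84.4% at 0.10 and 79.9% at 0.20.

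**The case against.** The strongest reply has four parts.

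- **No effect on the ratio is documented.** This stands. A reader might infer that the ratio does partly measure wasting or infection. The document supports only that it may. The same-visit link is also inferred from matching dates, and nothing is said about HIV counts or HIV care in this subgroup.
- **The sampling strata might already balance malnutrition or HIV.** The in-depth CICADA subset is stratified by prior malnutrition, so this is possible. The strata for Hypothesis 4 are not named, however, and strata used for selection belong in the model, which has only age and sex.
- **The general framework covers BMI and HIV, and BMI may be a mediator.** The mediation argument under Hypothesis 1 concerns BMI measured with the outcome, about four years after the ratio. BMI at the sampling visit is concurrent with the ratio. If impaired insulin secretion had itself lowered body weight, adjustment could remove some of the real signal, which is a reason to show both models.
- **Extra models are commonly left to an analysis plan.** That would answer a missing detail. Here the covariates are stated outright, with no later step as under Hypothesis 1.

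A reader might also infer that a null result could be a true association cancelled by wasting. Step 4 does not support that: under those assumptions the target effect is attenuated, not removed.

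**Conclusion.** The concern holds in a limited form. The stated Hypothesis 4 model omits BMI and HIV status at the time of the archived sample. For 280 members, about 14% of CICADA, low BMI was apparently concurrent with the ratio and not a past event. Given the protocol's own premises, the association may be partly confounded. Under the assumed effects the bias is from negligible to about a quarter of the 0.04 target, reaching a third only in the most extreme setting tried. The type I error in the main setting (14.5% v 7%) is 5.4% to 14.3%.

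This rests on the inferred same-visit link, on assumed shifts in the ratio, and on risks borrowed from Hypothesis 1. A reader might take the 44% as the share of the 120 sampled people who were affected; it is a share of recorded malnourished members only. Nor does the document support the conclusion that Hypothesis 4 would be uninterpretable whatever its result. The change is worth making because it is cheap and answers an obvious alternative explanation.

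**What to change.** 1. Name the sampling strata for the 60 cases and 60 controls, and include them in the model.
2. Add BMI and HIV status at the archived-sample visit, and CICADA subgroup, to the Hypothesis 4 logistic model. Alternatively, pre-state this as an adjusted model reported beside the age-and-sex model.
3. Pre-state a sensitivity analysis that excludes people with low BMI at that visit.
4. Keep any split by timing of malnutrition descriptive. With proportional sampling about 17 of the 120 would have concurrent low BMI (120 × 280/1951) and about 22 earlier malnutrition (120 × 355/1951). With 8 to 9 per arm, power for a 0.04 difference is only about 20%.
5. State that the sample, BMI and HIV status come from the same visit, if that is so.

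Cost: for the newest subgroup the variables appear to be on file. For TB-NUT and NUSTART members, BMI at that visit should be confirmed as available. A few more terms with 60 cases would lower power from about 88% to roughly 80–86% if they share 5–20% of the variation. Reporting the adjusted model second leaves the precision of the age-and-sex model unchanged.

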**: The sample size was a function of available cases and consumable costings. A sample of 120 (1:1 ratio of cases and controls) will provide 90% power to detect a difference of 0.04 in the fasting proinsulin/insulin ratio (assuming an SD of 0.07) which is smaller than that found between people with and without type 2 diabetes.
^
40
^

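### Hypothesis 4 is worded for previously malnourished adults, but its nested case-control sample and model cover all of CICADA, and the stated power applies only to the whole 60 v 60 comparison

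*Protocol article*

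**What the plan says.** All references are to the Protocol article.

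- **Hypothesis.** Under Study objectives and hypotheses, Hypothesis 4 reads: "An abnormal pro-insulin/insulin ratio is associated with later development of diabetes in adults who had malnutrition earlier in life", in connection with HIV or tuberculosis. The Statistical analyses section restates it: the ratio "is associated with later development of diabetes in adults who had malnutrition and infection".
- **Objective.** Specific objective 4, directly above the hypothesis, covers adults with or without HIV or earlier tuberculosis. It does not mention malnutrition. Nor do the Abstract's sentence on this component and secondary outcome 6 under Outcome measures.
- **Sample.** In the Hypothesis 4 analysis, "cases are 60 CICADA participants with current diabetes by OGTT and controls are 60 CICADA participants with normal OGTT". The next sentence adds: "These participants will be selected by stratified random sampling". The strata are not named.
- **Model.** "Logistic regression will be used, controlling for age and sex, to determine if prior proinsulin/insulin ratio is associated with later diabetes". Prior malnutrition is not a restriction, a covariate or an interaction.
- **Power.** With 120 people in all, half of them cases, the design "will provide 90% power to detect a difference of 0.04 in the fasting proinsulin/insulin ratio (assuming an SD of 0.07"). The same paragraph says that available cases and assay cost determined the sample size.
- **Cohort composition.** Table 1 gives the earlier BMI of the three CICADA subgroups. The text in the same row says that half of the TB-NUT group had BMI below 18.5, while the counts beside it give 147 of 450.

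**The concern.** The hypothesis names one population, and the sampling and the model address a wider one. Two consequences follow if the plan is carried out as written.

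First, an association estimated in a sample that may be two thirds not previously malnourished would be reported under a hypothesis about malnutrition. Without a malnutrition term, the model cannot show whether the ratio predicts diabetes in previously malnourished adults, or whether it does so differently in them.

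Second, a null result could be read as evidence about the malnourished with 90% power behind it. The power statement was not made for that group.

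**Working it through.** **1. The stated power.** Inputs from the Hypothesis 4 sample size paragraph: 60 per group, difference 0.04, SD 0.07. Two-sided 5% is an assumption, since no alpha is given for this calculation.

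- Standardised difference: 0.04 / 0.07 = 0.571.
- Normal approximation: power = Φ(0.04 / (0.07 × √(2/60)) − 1.96) = Φ(3.130 − 1.960) = Φ(1.170) = 87.9%.
- Noncentral t: 87.4%.
- Difference detectable with 90% power at 60 v 60: (1.960 + 1.282) × 0.07 × √(2/60) = 0.0414 (normal), or 0.0418 (t). Both print as 0.04.
- An SD of 0.067, which prints as 0.07, gives 90% for a difference of 0.04.
- A one-sided 5% test gives about 93%, so a one-sided test does not explain the 90%.

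The printed 90% is therefore not reproduced exactly, but rounding accounts for the gap.

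**2. Share of CICADA with prior malnutrition.** Counts from Table 1, taking BMI up to 18.5 as malnourished:

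| Subgroup | BMI <17 | BMI 17 to 18.5 | Total with BMI up to 18.5 |
|---|---|---|---|
| TB-NUT | 73 | 74 | 147 of 450 |
| NUSTART | 105 | 103 | 208 of 208 |
| New HIV +/- cohort | 109 | 171 | 280 of 1293 |
| All | 287 | 348 | 635 of 1951 (32.5%) |

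If cases and controls both mirrored this share, 60 × 0.325 = 19.5, so about 20 cases and 20 controls would be previously malnourished. Using the 50% quoted for TB-NUT instead (225 of 450) gives (225 + 208 + 280) / 1951 = 36.5%, or about 22 v 22.

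**3. Power for 0.04 within the previously malnourished** (noncentral t, two-sided 5%, SD 0.07). The protocol does not plan this test. The figures show only how far the stated power is from applying to it.

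| Composition of the sample | Malnourished cases v controls | Power |
|---|---|---|
| Mirrors Table 1 | 20 v 20 | 42% |
| TB-NUT share taken as 50% | 22 v 22 | 46% |
| Stratified half and half | 30 v 30 | 59% |
| Two thirds malnourished | 40 v 40 | 71% |
| All malnourished | 60 v 60 | 87% |

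At 20 v 20 the difference detectable with 90% power is 0.074; at 30 v 30 it is 0.060.

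**4. Population, element by element.**

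| Element | Population |
|---|---|
| Hypothesis 4 (both statements) | Previously malnourished adults, with infection |
| Specific objective 4 | Adults with or without HIV or earlier tuberculosis |
| Secondary outcome 6 | CICADA subset, no malnutrition criterion |
| Cases and controls | CICADA, no malnutrition criterion, strata unnamed |
| Model | Ratio, age and sex |

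The last four rows agree with each other. The first does not fit them.

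**The case against.** Four points stand against pressing this further.

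- **The power is right for the planned test.** The planned comparison is all 60 cases against all 60 controls, and the power statement describes it, apart from rounding. A reader might infer an arithmetic error in the 90%. The documents do not support that: the sample size was set by cases and cost, so 0.04 reads as a detectable difference given to two decimals, and 0.0418 prints as 0.04.
- **A reader might infer that Hypothesis 4 has only 42% power.** The documents do not fix that number. It belongs to an unplanned malnourished-only test and assumes that both groups mirror the historical Table 1 share. Expected SAMPA recruitment is 1412, of unknown composition. Equal shares also assume that malnutrition is unrelated to diabetes. If the Hypothesis 1 planning figures are used as a proxy (7% in those without malnutrition, and 7% + 7.5% = 14.5% in those with it), malnourished participants make up 0.325 × 0.145 / (0.325 × 0.145 + 0.675 × 0.07) = 50% of cases and 0.325 × 0.855 / (0.325 × 0.855 + 0.675 × 0.93) = 31% of controls. That is about 30 v 18, with power about 47%.
- **Sampling is stratified.** Prior malnutrition is the stratum for the in-depth subsets, and CT participants are chosen 50 exposed and 50 unexposed, so it could be a stratum here too. A condensed article may leave the strata to the full protocol. Even so, stratifying would not on its own settle the matter, because the stated model has no malnutrition term.
- **The objective does not require malnutrition.** Sample and model match Specific objective 4, the Abstract and secondary outcome 6.

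These points narrow the concern to a mismatch between the hypothesis wording and the sample and model. They do not remove it: the hypothesis is stated for the malnourished in two places, and the article itself gives the sampling source and the covariates.

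**Conclusion.** The planned analysis tests Specific objective 4 in CICADA as a whole and does not test Hypothesis 4 as worded. This rests on the text alone and needs no assumption.

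The stated power belongs to the whole 60 v 60 comparison. Two-sided at 5% with SD 0.07, it is 87% for 0.04 or 90% for 0.042, a rounding-level correction.

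For the previously malnourished alone, power for 0.04 depends on a composition that the protocol does not state: about 42% if the sample mirrors Table 1, 59% if it is split half and half, and 87% only if all 120 were previously malnourished. These figures are conditional and should not be quoted as the study's power. They show that a null result could not be taken as well-powered evidence about malnourished adults unless nearly all the sample came from that group.

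The point deserves correction before analysis. It concerns a secondary outcome and does not affect the primary outcomes.

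**What to change.** Choose one of two routes and name the sampling strata in either case.

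1. **Reword and extend the model.** State Hypothesis 4 for adults with or without prior malnutrition. Add prior malnutrition and its interaction with the proinsulin/insulin ratio to the logistic model, together with any stratification variables.
2. **Stratify.** Draw the same 120 samples stratified by prior malnutrition, and say that inference for the previously malnourished is a subgroup analysis.

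In both routes, say that the power statement applies to the whole 60 v 60 comparison only, and give it as 87% for 0.04 or 90% for 0.042 at SD 0.07. If a result for the malnourished is to be reported, give its power for the composition chosen (42% at 20 v 20, 59% at 30 v 30).

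The cost is wording, one or two more model terms with 60 cases, and, for the second route, a change to how the samples are drawn. No further assays are needed. The downside is that the interaction will be estimated imprecisely and should be reported with its confidence interval. A half-and-half split also depends on there being enough previously malnourished cases.
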